### Study design

This is a prospective, multicentre cohort study of patients diagnosed with LRR +/- DM with an evaluation of the oncological outcomes of the study cohort at 3 and 5 years. This will be a national research study in collaboration with the Association of Breast Surgery (ABS) Academic and Research committee, the Mammary Fold Academic and Research Collaborative (MFAC) committee and the UK Breast Cancer Trainees Research Collaborative Group (BCTRCG). The study has been adopted on to the National Institute for Health and Care Research (NIHR) clinical research network portfolio enabling research nurses at the participating sites to recruit study participants. The study has also been registered on the NIHR Associate Principal Investigator scheme.

The first phase of the study, the MARECA study national practice questionnaire (NPQ), consisted of scenario-based questions for the breast cancer multidisciplinary teams (MDTs) at the participating centres. The published results^14^ of the NPQ documented the current stated practice of breast cancer LRR management by MDTs, and captured data on practice variations and areas of uncertainty in patient management.

The second phase of the study, the national prospective cohort study, aims to recruit at least 500 women and men newly diagnosed with breast cancer LRR across 50 UK breast units. Recruitment is over a 24 months period. The study has been approved by the London - Brighton & Sussex Research Ethics Committee (21/PR/1128), with the first MREC approval date 07/09/2021 and is a registered clinical trial (ISRCTN11908093). The study recruited its first study participant in January 2022.

### Study setting

We will identify and recruit study participants from breast services at NHS hospitals in all four nations of the UK.

### Study participants

Female or male patients who were previously treated for breast cancer with curative intent and who have recently (within 6 months) been diagnosed with a breast cancer LRR +/- DM. Full inclusion and exclusion criteria are shown in Tables 1 and 2. For the purpose of this study, LRR is defined as a histological diagnosis of invasive breast cancer or ductal carcinoma in situ in the ipsilateral breast (if applicable)/skin/chest wall/regional nodes (axilla/internal mammary/supraclavicular/infraclavicular) following previous breast cancer treatment with curative intent.

**Table 1 T1:** Inclusion criteria.

Inclusion criteria
• Female or male patients more than 18 years old
• Treated for previous unilateral or bilateral breast cancer (invasive cancer including all histological subtypes as well as ductal carcinoma in situ) with curative intent
• No previous evidence of distant metastatic disease
• Recently (within the last 6 months) diagnosed with new ipsilateral breast cancer LRR (biopsy proven invasive cancer including all histological subtypes or ductal carcinoma in situ) +/- distant metastasis
• Able to provide written informed consent
• A minimum of 3 months interval between the resection surgery for the original cancer and the diagnosis of LRR. There will be no maximum interval time period

**Table 2 T2:** Exclusion criteria.

Exclusion criteria
• Patients where the new breast cancer diagnosis is in the contralateral breast
• For patients who present with new bilateral breast cancer, the side with no previous cancer will be excluded
• Patients diagnosed with distant metastatic disease with no evidence of LRR
• Patients diagnosed with angiosarcoma
• Patients with previous history of non-breast cancer treatment that was noncurative in intent
• Patients who have had previous ipsilateral surgery for atypia, benign conditions, or phyllodes tumour and other breast sarcomas AND no previous ipsilateral primary breast cancer resection
• Patients under 18 years old
• Patients lacking capacity to provide written informed consent

### Study processes

Eligible patients recently (within the last 6 months) diagnosed with LRR will be identified by healthcare professionals directly involved in the patient’s care:at breast MDT meetings;in breast surgery and oncology clinics;by screening patent records.

The approach will be undertaken via two routes:An appropriately trained member of the team (as per the delegation log), at each unit will approach eligible patients and discuss the option of study participation and provide a study patient information sheet (PIS).Identified patients may also be approached using the approved invite letter, which is posted to patients along with the PIS.

The completion of the consent form may occur during the patient’s scheduled hospital visits. In addition, patients may also consent by post following invite in person or having been approached by the approved invite letter. All study participants are invited to consider consenting to an optional tissue sub-study. This does not involve the collection of any new tissue, but requests participants’ permission to collect pre-existing samples from their original cancer and recurrence. A translational tissue sub-study is planned and will be based on the uptake rate of this optional consent.

### Study data collection

Data regarding tumour characteristics, investigations performed and treatment details for the patient’s original and recurrent cancer will be collected. Data collection will involve recording patient data that are routinely collected as part of standard clinical practice. Study data will be collected and managed using REDCap^18,19^ (Research Electronic Data Capture) electronic data capture tools The required data fields for the MARECA study prospective cohort study are summarised in the protocol appendices (Supplementary Data File, Supplemental Digital Content 1, http://links.lww.com/JS9/B670).

The collection of oncological outcome data at 3 and 5 years (Fig. 1) post diagnosis will enable the determination of the DFS, PFS and OS of the study cohort. Data collection will include the patient’s survival status, and whether death was related to breast cancer or not, and the date of death. Data on the occurrence of any further LRR or DM, and respective dates will also be collected. To gather these data, the participating units will access their hospital electronic database and hence no direct patient contact is anticipated as part of the study procedure.

**Figure 1 F1:**
[figure not shown]
MARECA study flowchart.

### Anticipated recruitment and sample size

Out of 144 breast units in the UK, 50 units have agreed to participate in the MARECA study. Based on the MARECA study NPQ results^14^, we would anticipate each unit to recruit 5 to 10 patients over 12 months. Therefore, the study aims to recruit at least 500 patients diagnosed with LRR +/- DM over 24 months. The study’s primary endpoint is to determine whether patient prognosis after their LRR diagnosis (without DM) differs according to the type of breast cancer surgery (mastectomy versus BCS and radiotherapy) for the original cancer. To determine the primary endpoint, logistic regression analysis was used to determine the effect of treatment type (mastectomy versus BCS and radiotherapy for the original cancer) on DFS by adjusting for other covariates (including tumour stage, node stage, tumour receptor status and tumour grade). This analysis determined that the sample size for each group would be 165 patients. Therefore, a subset of 330 patients diagnosed with LRR (without DM) will require recruiting to the study to determine the study’s primary endpoint. This falls within the minimum patient recruitment target of 500 patients.

As of 11/12/23, the study has recruited 684 patients and hence exceeded the minimum recruitment target of 500 patients. During the recruitment process, we identified that the number of patients treated with BCS for the original cancer was higher than those treated with mastectomy for the original cancer. Therefore, once we reached the overall recruitment target of 500 patients earlier in 2023, the decision was made to continue recruitment and thereby enable the minimum number of patients in each treatment arm to be reached to determine the study’s primary endpoint.

### Statistical analysis

The study report will be prepared according to the STROBE (Strengthening the Reporting of Observational Studies in Epidemiology) reporting guidelines for observational studies^20^. CONSORT (Consolidated Standards of Reporting Trials) will be used to monitor data completeness from eligibility screening, approach, study acceptance and final follow-up. Analyses will be performed according to the statistical analysis plan. All data analysis will occur centrally and will be led by the study steering group.

Simple summary statistics will be calculated to describe demographic, procedure and outcome data, overall and at the individual site level. Data will be tested for distribution and differences between groups using unpaired *t*-tests, Mann–Whitney *U* tests and *χ*
^2^ tests, as appropriate. Kaplan–Meier survival analysis will be performed at the two study time points (3 and 5 years after the diagnosis of LRR). Cox proportional hazards multivariate regression analysis and log-rank tests for univariate analysis will be performed to include potential prognostic factors as variables of interest.

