## Discussion

The MARECA study is the first in the UK, which aims to determine the current management of breast cancer LRR across participating sites, explore investigations utilised, study cancer progression and treatment patterns, as well as potential variations in patient management. The MARECA study NPQ result^14^ has already demonstrated variation in certain aspects of patient management as stated by the participating breast MDTs. The planned sample size would create the largest prospective study cohort of patients diagnosed with LRR in the UK.

There are current uncertainties in the management of patients diagnosed with LRR. Patients may be classified as having a TR or a NP breast cancer. This classification is not routinely performed across UK breast units as its clinical implications remain uncertain. The collation of this study cohort enables the opportunity to use existing clinical classifications, determine what proportion of patients are diagnosed with a TR as opposed to a NP, and explore if these clinical classifications predict the patient’s subsequent prognosis. In addition, the uptake rate of the optional consent to donate archived tissue will facilitate the design of the tissue sub-study, which aims to refine the distinction between a TR and a NP, using molecular assays. The combined clinical and molecular information will enable further stratification of breast cancer LRR with an aim of delivering a more tailored treatment whilst optimising survival outcome.

The study will describe what proportion of patients diagnosed with LRR undergo radiological staging investigations, which imaging modalities are utilised, and the proportion of patients found to have associated DM at presentation. The study will explore and aim to identify a patient subgroup where routine staging investigations may not be required given the low pick-up rate of DM, with associated cost benefits to the healthcare system.

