There are potential limitations to the study’s design. The study is recruiting patients from UK breast units with varying number of breast cancer patients treated in each participating centres. Therefore, some units may be better represented than others. It is also unknown whether the COVID-19 pandemic and the required alterations in the management of primary breast cancer^23^, may impact on how patients are presenting with LRR, and whether there is a delay in diagnosis with a higher rate of associated DM. Lastly, it is also uncertain whether the patient uptake rate to the study may be higher in those found to have isolated LRR, as opposed to LRR with associated DM. There may be less inclination by the clinical team to approach the latter patient group, or these patients may be less willing to participate due to the noncurative nature of their disease. We also currently do not know the differential prognosis or the proportion of LRR patients diagnosed with different tumour subtypes. It maybe that based on the results of the 5-year survival analysis, an ethics amendment would be considered to follow-up particular subgroup (e.g. lobular breast cancer) of the study cohort for a longer period of time.

In conclusion, this prospective, multicentre cohort study will examine the current management and outcomes of patients diagnosed with breast cancer LRR in the UK. The resulting data will inform future research and support the development of best practice guidelines for this patient group.

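### The named tests treat patients as independent and use unit only descriptively, so comparisons of management variables that follow unit practice can exceed their nominal level, and pooled proportions generalised nationally would look too precise

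*Protocol article*

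**What the plan says.** The Statistical analysis section names its methods. For group comparisons: "Data will be tested for distribution and differences between groups using unpaired" t-tests, Mann–Whitney U and chi-square tests, as appropriate. For outcomes: "Cox proportional hazards multivariate regression analysis and log-rank tests for univariate analysis will be performed to include potential prognostic factors". Unit appears once, in the summary statistics, which are given "overall and at the individual site level". The section does not define the groups to be compared and mentions no confidence intervals. It also states: "Analyses will be performed according to the statistical analysis plan". That plan is not available here.

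Three other statements bear on independence:

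- Anticipated recruitment and sample size: "50 units have agreed to participate in the MARECA study", and "we would anticipate each unit to recruit 5 to 10 patients over 12 months".
- Discussion, on the national practice questionnaire: it "has already demonstrated variation in certain aspects of patient management as stated by the participating breast MDTs".
- Discussion, limitations: because units differ in volume, "some units may be better represented than others". No consequence for the analysis is drawn.

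**The concern.** Describing management is the first task set for the cohort: staging, repeat breast conserving surgery (BCS), repeat sentinel node biopsy, systemic therapy and radiotherapy. These decisions are made with a unit's multidisciplinary team, so patients of one unit may resemble each other more than patients of different units. The Discussion also plans to compare outcomes after repeat BCS with outcomes after mastectomy for the recurrence, and the choice between these may partly be unit policy.

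Two things are at stake. A test of association between two variables that both follow unit habit can report that habit as a patient-level association. And a pooled proportion presented as UK practice can appear better known than it is. Both matter because the results are meant to feed national guidelines.

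**Working it through.** **Inputs from the article.** 50 units; 684 patients recruited by 11/12/23; 5 to 10 patients per unit per year. The accrual figure reproduces the recruitment target: 50 × 5 × 2 = 500 at the lower end and 50 × 10 × 2 = 1000 at the upper. Mean unit size m = 684/50 = 13.68. The 165 per group cannot be reproduced, because no alpha, power, effect size or event rate is stated; nothing below depends on it.

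**Assumptions.** The article gives no ICC, so a range of 0.01 to 0.20 is used. It gives no spread of unit sizes, so the range runs from equal units (CV 0) to CV 0.7. Two-sided 5% level.

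**1. Pooled proportion, generalised beyond the participating units.**
Design effect DE = 1 + (m(1 + CV²) − 1) × ICC.
Equal units: m − 1 = 12.68. CV 0.7: 13.68 × 1.49 − 1 = 19.38.

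| ICC | DE, equal units | DE, CV 0.7 | True SE ÷ naive SE |
|---|---|---|---|
| 0.01 | 1.13 | 1.19 | 1.06–1.09 |
| 0.05 | 1.63 | 1.97 | 1.28–1.40 |
| 0.10 | 2.27 | 2.94 | 1.51–1.71 |
| 0.20 | 3.54 | 4.88 | 1.88–2.21 |

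With equal units, the effective sample size out of 684 is 607, 419, 302 and 193.

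**2. Chi-square test of a patient-level factor.** What matters here is the product of the two ICCs. The approximate variance inflation is 1 + (m(1 + CV²) − 1) × ICC(factor) × ICC(outcome), and the true level is 2[1 − Φ(1.96/√inflation)].

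- Both ICCs 0.1: inflation 1 + 12.68 × 0.01 = 1.127, level 6.5% with equal units; 1.194 and 7.3% at CV 0.7.
- Both ICCs 0.2: inflation 1 + 12.68 × 0.04 = 1.507, level 11.0%; 1.775 and 14.1% at CV 0.7.
- Factor 0.1, outcome 0.02: inflation 1.025, level 5.3%; 1.039 and 5.4–5.5% at CV 0.7.
- Factor ICC 0: inflation 1, level 5%.

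Simulation (50 units, 684 patients, beta-distributed unit probabilities with mean 0.3 for the factor and 0.4 for the outcome, 20,000 replicates) gave:

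| ICC factor / outcome | Equal units | CV 0.7 |
|---|---|---|
| 0.1 / 0.1 | 6.6% | 7.3% |
| 0.2 / 0.2 | 10.9% | 13.6% |
| 0.1 / 0.02 | 5.2% | 5.5% |
| 0 / 0.1 | 4.9% | 5.2% |

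Other runs of the same design ranged from 6.0% to 7.3% for the first row and from 11% to 14.5% for the second.

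**3. Cases with no inflation.** In a simulation of 50 units of 14 patients with outcome ICC 0.05 to 0.20, a factor that varies at random within units gave levels of 5.1% to 4.5%. A factor balanced within every unit gave 4.6% to 3.0%, which is conservative. A chi-square test comparing the units themselves held its level at 4.8%.

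**4. Primary contrast.** For 330 patients, m = 330/50 = 6.6. Even if original surgery had ICC 0.1 and the outcome 0.02, the inflation with equal units would be 1 + 5.6 × 0.002 = 1.011, a level of about 5.1%.

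**The case against.** The strongest objection is that the article defers to a statistical analysis plan, which may already account for unit; naming Cox regression does not rule out a robust variance or a frailty. That stands as far as it goes: nobody can infer from the article that clustering is unplanned. But the article does not leave the tests open. It names independent-sample tests, and a plan that handled clustering would have to go beyond them.

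Further objections stand and narrow the point:

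- A reader might infer that all p-values are too small. The calculations contradict this. Inflation needs both variables to cluster by unit, and the article does not say which groups will be compared.
- A reader might infer that every listed management variable is known to differ between units. The article reports variation only in certain aspects, as stated by teams in a survey. It gives no measured patient-level variation.
- No intervals are announced, so the design effects apply to any that are reported, not to a stated plan.
- The aim is worded for the units taking part. For that target, with those units fixed, between-unit variance does not widen the interval. It does once the result is read as national practice. The units volunteered, and a cluster-robust interval does not cure that selection.
- CV 0.7 is on the high side of what 5 to 10 patients a year suggests. Subsets such as repeat BCS have fewer patients per unit, as would more than 50 units, the number given in the abstract. All of this pulls the figures towards or below the lower end.

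**Conclusion.** The point holds in a limited form. The named methods make no allowance for unit, although the article itself gives reasons to expect clustering in some management variables.

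For comparisons where factor and compared variable both follow unit practice, the true level of a 5% test is about 6–7% if both ICCs are 0.1 and roughly 11–13% if both are 0.2, with single runs up to 14.5%. It is about nominal if the factor does not vary by unit or the outcome ICC is near 0.02. Precision of a pooled proportion taken as national practice is overstated by a factor of about 1.1 in the standard error at ICC 0.01 and up to about 1.7 at 0.10. These sizes rest on assumed ICCs, 50 units, 684 patients and an assumed CV between 0 and 0.7.

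A reader might conclude that the primary comparison is invalid or under-powered for this reason. The document gives no support for that: original surgery is a patient-level factor that can be expected to mix within units, and neither that contrast nor the 165 per group is materially affected. The change is worth making before the 3-year and 5-year analyses, but it is a moderate point.

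**What to change.** State in the analysis plan, or confirm if it is already there:

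- For comparisons involving management variables, such as repeat BCS versus mastectomy for the recurrence, use logistic or linear models with a unit random effect, or GEE with cluster-robust errors, in place of the simple tests. State which is chosen, because the two estimate different effects for binary outcomes.
- Give the Cox models a unit-clustered robust variance or a shared frailty. Avoid stratifying by about 50 small units: at about 6.6 patients per unit in the primary subset this discards information, and units with only one type of original surgery would contribute nothing to that contrast.
- Use cluster-robust intervals for any pooled proportion presented as national practice. Where a figure describes only the participating units, say so.
- Report the estimated ICCs of the main management variables, so that readers can judge the assumed range.

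Simple tests can stay for patient-level factors with no plausible link to unit. No new data are needed, since site-level summaries are already planned and unit must therefore be identifiable. The cost is slightly more analysis work and somewhat wider intervals.

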### Data validation and management

Data collection will occur in accordance with Good Clinical Practice (GCP), Caldicott principles and the General Data Protection Regulation (GDPR) 2018 and will work in line with NHS confidentiality guidelines and codes of conduct. Data for each patient will be pseudonymised using a unique alphanumeric study identification number. No patient identifiers other than the study number will be recorded in the REDCap database (the eCRF for the study). The local PI will keep a secure record of the RedCap ID with the corresponding NHS number (in England and Wales), Community Health Index number (in Scotland), or Health and Care number (in Northern Ireland). This is required for the research team at each participating centres to access the hospital electronic system at 3 and 5 years after LRR diagnosis to record oncological outcomes.

### Patient and public involvement

Cancer recurrence and long-term outcomes of treatment were key themes that emerged from the National Cancer Research Institute’s ‘living with and beyond cancer research priorities’ project https://www.ncri.org.uk/lwbc/, which surveyed over 3500 patients, carers and health and social care professionals. Furthermore, a James Lind Alliance priority setting partnership in breast surgery identified breast cancer recurrence as one of top 10 research priorities by both patients and healthcare professionals^21^. We have gained valuable input from a patient representative group (Independent Cancer Patients’ Voice, ICPV; PF, as a representative of the ICPV, is a member of the study steering group), especially in drafting the PIS and the consent form. Patient involvement will play a key part in design of the data analysis and dissemination plans.

## Discussion

The MARECA study is the first in the UK, which aims to determine the current management of breast cancer LRR across participating sites, explore investigations utilised, study cancer progression and treatment patterns, as well as potential variations in patient management. The MARECA study NPQ result^14^ has already demonstrated variation in certain aspects of patient management as stated by the participating breast MDTs. The planned sample size would create the largest prospective study cohort of patients diagnosed with LRR in the UK.

There are current uncertainties in the management of patients diagnosed with LRR. Patients may be classified as having a TR or a NP breast cancer. This classification is not routinely performed across UK breast units as its clinical implications remain uncertain. The collation of this study cohort enables the opportunity to use existing clinical classifications, determine what proportion of patients are diagnosed with a TR as opposed to a NP, and explore if these clinical classifications predict the patient’s subsequent prognosis. In addition, the uptake rate of the optional consent to donate archived tissue will facilitate the design of the tissue sub-study, which aims to refine the distinction between a TR and a NP, using molecular assays. The combined clinical and molecular information will enable further stratification of breast cancer LRR with an aim of delivering a more tailored treatment whilst optimising survival outcome.

The study will describe what proportion of patients diagnosed with LRR undergo radiological staging investigations, which imaging modalities are utilised, and the proportion of patients found to have associated DM at presentation. The study will explore and aim to identify a patient subgroup where routine staging investigations may not be required given the low pick-up rate of DM, with associated cost benefits to the healthcare system.

The study aims to provide data on which patient could be offered repeat BCS for LRR, how many patients are currently managed with repeat BCS, and how their outcomes compare against those undergoing mastectomy for LRR. The data from the MARECA study may inform the design of future trials exploring the role of repeat BCS for LRR. A repeat sentinel lymph node biopsy is offered when patients are diagnosed with LRR with a normal preoperative clinical assessment of the ipsilateral axillary lymph nodes. However, the methods of SLN relocalisation, the success rate of SLN reidentification and its long-term prognostic impact at the national level remains unexplored. The MARECA study is designed to gather such information, which will be valuable in setting future guidelines.

LRR may be due to the survival and proliferation of clones that are resistant to a range of adjuvant therapies used to treat primary breast cancer. Therefore, it is important to examine the choice of endocrine and/or chemotherapy in patients with LRR. CALOR trial^22^ demonstrated that patients with ER-negative LRR benefit from chemotherapy, but those with ER-positive LRRs do not. However, compared to treatment for primary breast cancer, there is a relative lack of clinical trial data on the efficacy of further adjuvant systemic therapy in patients diagnosed with LRR. The MARECA study will therefore gather data on the type of adjuvant treatments currently used to treat patients diagnosed with LRR in the UK.

There are potential limitations to the study’s design. The study is recruiting patients from UK breast units with varying number of breast cancer patients treated in each participating centres. Therefore, some units may be better represented than others. It is also unknown whether the COVID-19 pandemic and the required alterations in the management of primary breast cancer^23^, may impact on how patients are presenting with LRR, and whether there is a delay in diagnosis with a higher rate of associated DM. Lastly, it is also uncertain whether the patient uptake rate to the study may be higher in those found to have isolated LRR, as opposed to LRR with associated DM. There may be less inclination by the clinical team to approach the latter patient group, or these patients may be less willing to participate due to the noncurative nature of their disease. We also currently do not know the differential prognosis or the proportion of LRR patients diagnosed with different tumour subtypes. It maybe that based on the results of the 5-year survival analysis, an ethics amendment would be considered to follow-up particular subgroup (e.g. lobular breast cancer) of the study cohort for a longer period of time.

In conclusion, this prospective, multicentre cohort study will examine the current management and outcomes of patients diagnosed with breast cancer LRR in the UK. The resulting data will inform future research and support the development of best practice guidelines for this patient group.

